##### Self-Reported Adherence

Self-reported medication adherence will be assessed at baseline and weeks 2, 8, 13, 26, 39, and 52, with the Adherence to Refills and Medication Scale, a validated and widely used self-report measure [29].

##### Medication Adherence Assay

Blood samples are drawn at baseline and follow-up visits at weeks 13, 26, 39, and 52, and a liquid chromatography mass spectrometry (LC-MS) assay developed by Precera Bioscience, Inc (Brentwood, TN) is used to detect several hundred prescription medications, over-the-counter medications, and medication metabolites in each patient sample received (including all drugs incorporated into our treatment algorithm) in participant blood samples. This serves as a direct, objective assessment of medication presence and levels to measure medication adherence. This assessment will be compared with other measures of medication adherence. The assay imparts limited burden on participants, as it requires only 100 microliters of serum or plasma. Unpublished data from our previous work have shown that there is a negative relationship between assay adherence and change in SBP among patients prescribed less than or equal to 3 antihypertensive medications (Figure 3) [30].

#### Self-Efficacies for Behavior Change

We collect various measures of self-efficacy for our target behavior changes at baseline and weeks 13, 26, 39, and 52, including physical activity via the Exercise Self-Efficacy Scale [31], medication adherence via the Medication Adherence Self-Efficacy Scale [32], and diet using an investigator-developed 11-item instrument assessing confidence in reducing sodium consumption, avoiding high-fat foods, avoiding sugar-sweetened beverages, and improving vegetable and legume intake.

#### Additional Health Measures

In addition to measures focused on specific behavior changes, we will also measure patient activation with the Patient Activation Measure [33], HTN knowledge with the 14-item Hypertension Evaluation of Lifestyle and Management Knowledge Scale [34], and functional status using the 12-Item Short-Form Health Survey (SF-12) at baseline and weeks 13, 26, 39, and 52 [35]. Additionally, we will measure health literacy via the 7-item Rapid Estimate of Adult Literacy in Medicine-Short Form at baseline [36], a modified Sugar-Sweetened Beverages measure at baseline and weeks 26 and 52 [37], and patient perceptions of the LC-MS assay for medication adherence, using investigator-developed questions, at week 52.

**Figure 3 figure3:**
[figure not shown]
Association between assay adherence and change in systolic blood pressure (unpublished data from previous work). SBP: systolic blood pressure.

#### Technology-Related Measures (MI-BP Group Only)

To help put into context the intervention-group outcomes, we will assess several different technology-related measures, including technology acceptance (among the MI-BP participants only) via measures adapted from the Technology Acceptance Model by Davis that looks at participant perceptions of the perceived ease of use and perceived usefulness of MI-BP at weeks 13, 26, 39, and 52 [38]. We will also assess participant perceptions of the MI-BP intervention. Finally, MI-BP utilization will be assessed through usage log analysis at the end of the study.

### Statistical Analysis Plan

#### Analysis of Blood Pressure Control

To determine the effect of MI-BP on BP at 1 year (aim 1) and to determine whether BP control is better in intervention-group participants compared with controls (hypotheses 1a), we will conduct a comparative analysis using a logistic regression with BP control as the outcome and study arm as the primary factor, controlling for demographic characteristics such as age, gender, medical history, baseline levels of functional status, health literacy, HTN knowledge, self-efficacy, and baseline BP at randomization. To determine whether mean SBP is better in the intervention group, compared with controls (hypothesis 1b), differential reduction in the coprimary outcome of SBP will be assessed in a linear mixed-effects regression framework, with time (baseline and end-of-trial), group, and time-by-group interaction as the primary independent variables. The subject-level characteristics used in the analysis of the primary outcome will be controlled in the regression model.

To determine the effect of MI-BP on secondary outcomes (aim 2), we will also use linear mixed-effects regression models with the secondary outcomes of interest as the dependent variables and week (as a continuous variable), study group, and week-by-group interaction as the primary independent variables. All appropriate model diagnostics will be carried out.

During data analysis, we will statistically address missing data resulting from incomplete data collection or participant attrition using the multiple imputation technique. Missing values will be imputed by repeatedly and iteratively fitting a sequence of regression models; it is a technique that is flexible in allowing different types of variables (categorical and continuous) to be imputed together without requiring any multivariate joint distributional assumption. Missing values are sequentially updated using bootstrap or Markov Chain Monte Carlo based on multiple regression models with other variables as covariates. This procedure will be conducted for 10 repetitions or cycles, a number considered adequate for most applications, thereby constructing an *imputed* dataset. Results from the 10 regressions will be combined with the imputed data using Rubin’s formula [39].

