### Sample Size

On the basis of data from our previous studies, we estimate that 30% of usual-care participants will achieve BP control (BP<130/80 mmHg) by 1 year. We consider at least 17.5% higher control rates for the intervention arm to be clinically meaningful. On the basis of a 2-sided chi-square test of comparing 2 proportions at a 5% level of significance, the power for detecting the difference between MI-BP self-monitoring arm and usual care is 90%, with 161 participants per arm. Allowing for 19% attrition based on our previous work in similar patient populations, we plan to recruit 198 participants per arm, for a total of 396 participants. It is anticipated that at the end of trial, both groups will improve on average SBP. We estimate a 10- and 17- point drop in the usual care and MI-BP arms, respectively, at 1 year. Further, a constant between-subject SD of 10 mmHg is assumed, along with an intra-subject correlation of 0.5. With 161 subjects per arm, we can detect a group-by-time interaction with power >95% at 5% level of significance.

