### Procedures

Once enrolled and consented in the ED (weeks −1 to −2), participants are scheduled for a return visit in 1 to 2 weeks for their baseline appointment (week 0) at the WSU CRSC. As noted above, only those individuals with persistent uncontrolled HTN at this visit are eligible to remain in the study. Baseline data collection also occurs at week 0, and participants are given a prescription for antihypertensive therapy, and referrals to primary care are made by study physicians. For the participants already taking antihypertensive medications and who have an existing relationship with a primary care provider (PCP), we contact their PCP to inform them of our algorithm-based approach to antihypertensive therapy and work to coordinate any medication adjustments. In week 2, participants undergo medication titration, the process of adjusting antihypertensive medication dosages to ensure appropriate and optimal treatment, and are then randomized into 1 of the 2 study arms. Please see Multimedia Appendix 2 for the medication algorithm used in this trial for titration. From our previous unpublished work, we have determined that attrition is greatest between ED recruitment and the first follow-up visit. Thus, by delaying randomization until after this run-in period, we anticipate fewer participants will be lost to follow-up. Moreover, to reduce attrition, at baseline, we collect contact information for up to 3 alternate contacts, who we may call if we are unable to locate the participant to schedule data collection visits. Our staff also heavily rely on telephone calls and text messaging to participant smartphones to communicate as needed to coordinate scheduling, which tend to be the preferred modes of communication among participants. If needed and requested by participants, we also provide transportation to data collection visits. The MI-BP study staff take a participant-centered approach to trial management and are available daily to meet participant needs. Participants are encouraged to call the staff for any questions pertaining to their medications, their BP, technical issues with the intervention, or other issues that arise (see Figure 2 for a flow diagram of trial procedures). Peer-review report from the Center for Scientific Review has been provided in Multimedia Appendix 3.

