#### Blood Pressure

We are collecting 2 types of BP data in this trial: in-clinic and home BPs. In-clinic BPs are assessed for every patient, regardless of trial arm, at every study visit by a trained study staff member using a BpTRU BP monitoring device. Home BP data are also collected from the intervention-group participants as a part of their use of the MI-BP app.

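### The coprimary SBP model has baseline SBP as a response row and also carries over a baseline-BP covariate, which cancels from the tested interaction, so the test gains nothing from baseline adjustment

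*Protocol article*

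**What the plan says.** All of this is in the protocol article.

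- **SBP model** (Statistical Analysis Plan, Analysis of Blood Pressure Control): a "linear mixed-effects regression framework, with time (baseline and end-of-trial), group, and time-by-group interaction as the primary independent variables". Each person contributes a baseline row and an end-of-trial row, and the interaction carries the test.
- **Covariates of the BP-control logistic model** (same section): these include "baseline levels of functional status, health literacy, HTN knowledge, self-efficacy, and baseline BP at randomization".
- **Carry-over to the SBP model** (same section): "The subject-level characteristics used in the analysis of the primary outcome will be controlled in the regression model". Baseline BP is not excepted, and no random-effects or covariance structure is named.
- **Missing data** (same section): multiple imputation, so each analysed data set is complete.
- **Timing** (Procedures): "Baseline data collection also occurs at week 0", whereas randomization follows in week 2, after titration. The Blood Pressure section adds: "In-clinic BPs are assessed for every patient, regardless of trial arm, at every study visit". A week-0 and a week-2 reading should therefore both exist.
- **Planning values** (Sample Size): "We estimate a 10- and 17- point drop in the usual care and MI-BP arms, respectively, at 1 year", with a constant SD of 10 mmHg, a within-subject correlation of 0.5, 161 analysed per arm, and power above 95% for the group-by-time interaction.

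**The concern.** Read as written, baseline BP stands on both sides of a coprimary model. A reader would expect an SBP test adjusted for baseline. A covariate that is constant within a person cannot adjust a time-by-group contrast when both rows are present, so that adjustment does not happen.

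The text also leaves open which reading is meant. The baseline row points to week 0, while the covariate is described as BP at randomization, which points to week 2. This matters beyond tidiness, because one of the two readings can also disturb the standard error. At stake are precision that costs nothing to recover and, under particular conditions, the size of a coprimary test.

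**Working it through.** **Inputs.** From Sample Size: SD 10 at both times, r = 0.5, n = 161 per arm, difference 17 − 10 = 7 mmHg. Assumed: normal data, a two-sided 5% test, complete pairs.

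**1. The plan's own figure.** SD of change = 10 × √(2(1 − 0.5)) = 10, so SE = 10 × √(2/161) = 1.115. Then 7/1.115 = 6.28, and power = Φ(6.28 − 1.96) > 99.9%. If SD 10 is read as the random-intercept SD only (total variance 200), power is 99.3%. Both agree with the stated figure of more than 95%.

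**2. The covariate cancels.** For person i, write y(i,t) = … + βx(i) + …, with x(i) the same in both rows. In y(i,1) − y(i,0) the term βx(i) drops out, and the interaction equals the difference in mean change. This holds for the week-0 reading, the week-2 reading and every other subject-level main effect in the list. Four simulated data sets fitted as mixed models agreed. In one, the interaction was −7.365 with the covariate, −7.365 without it and −7.365 as the raw difference in change, while ANCOVA gave −7.822.

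**3. The cost in precision.**
- Change score: variance 100, SE 1.115.
- ANCOVA: variance 100 × (1 − 0.5²) = 75, SE = √(2 × 75/161) = 0.965.
- Variance ratio 100/75 = 1.33, so 33% more variance.
- With equal SDs the ratio is 2/(1 + r): 1.54 at r = 0.3 and 1.18 at r = 0.7.

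If the follow-up SD is larger (assumed values; baseline SD 10, r = 0.5):

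| Follow-up SD | Change variance | ANCOVA variance | Excess |
|---|---|---|---|
| 10 | 100 | 75 | 33% |
| 12 | 100 + 144 − 120 = 124 | 0.75 × 144 = 108 | 15% |
| 15 | 100 + 225 − 150 = 175 | 0.75 × 225 = 168.75 | 4% |
| 20 | 100 + 400 − 200 = 300 | 0.75 × 400 = 300 | 0% |

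**4. The standard error if row and covariate are the same reading.** The shared slope averages 1 (baseline row) and 0.5 (week-52 row), giving 0.75.
- Residual variance at baseline: 0.25² × 100 = 6.25.
- Residual variance at week 52: 0.25² × 100 + 75 = 81.25.
- Within-person covariance: 0.25 × (−0.25) × 100 = −6.25.

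A random intercept cannot produce a negative covariance, so its variance is estimated at zero. The pooled residual variance is (6.25 + 81.25)/2 = 43.75, where 100/2 = 50 is needed. Reported/true SE = √(43.75/50) = 0.935, or 1.04 against 1.115. Type I error = 2(1 − Φ(1.96 × 0.935)) = 6.7%.

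In general, with equal SDs, the ratio is √((3 + r)/4). Type I error is then 7.5%, 6.7% and 5.9% at r = 0.3, 0.5 and 0.7. Simulating 20,000 null trials per setting gave 7.5%, 6.9% and 6.0%, with the intercept variance at zero in every trial.

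**5. The standard error if the covariate is a separate week-2 reading.** Assuming it is equally correlated with both rows, 6,000 null trials per setting gave 4.8% to 5.1%. The SE is valid, and the covariate still adds nothing.

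**The case against.** A two-time-point group-by-time interaction is a valid, unbiased test in a randomized trial. It matches the power calculation, and power exceeds 99.9% with either SE, so no stated objective is at risk. All of this stands. The point concerns efficiency and an adjustment that is promised but has no effect.

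A reader might go further in four ways that the article does not support.

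- **That type I error is inflated.** This needs the same reading in both places and a random intercept bounded at zero. The article names no covariance structure, which an article may leave to the full plan, and its wording is open to a separate week-2 reading. With that reading, or with a structure that allows negative within-person covariance, the SE is correct. The inflation also shrinks if follow-up SBP is more variable: about 5.8% at SD 12, 5.2% at SD 15 and none at SD 20.
- **That the 33% is fixed.** It follows from the plan's constant SD. Eligibility excludes SBP below 130 mmHg at the baseline visit, which truncates baseline but not follow-up, so a larger follow-up SD is plausible.
- **That leaving out weeks 8 to 39 loses information.** The hypothesis concerns 1 year. Intermediate readings help mainly where week 52 is missing, and the plan handles that by multiple imputation. No loss has been shown.
- **That a week-0 baseline is an untreated value or biases the test.** Procedures provides for participants already on antihypertensives, and week 0 precedes randomization.

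**Conclusion.** The point holds as one of efficiency and clarity. Whichever BP reading is meant, the carried-over covariate has no effect on the coprimary SBP test, which is an unadjusted change-score comparison. Under the plan's own assumptions the SE is 1.115 mmHg where ANCOVA gives 0.965. The gap narrows as follow-up SD rises above baseline SD.

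A modestly anti-conservative test, about 6.7% instead of 5%, is possible under the two joint conditions in step 4. It should be described as conditional. The choice of baseline reading helps decide whether it arises, so that choice should be fixed before data are examined.

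The sample size rests on BP control: 30% against 47.5% with 161 per arm reproduces 90% power. It is unaffected, as is the SBP power statement. This is worth correcting but does not threaten the trial.

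**What to change.** 1. State whether baseline SBP is the week-0 or the week-2 pre-randomization BpTRU reading, and use that definition in both coprimary models.
2. For SBP, do one of the following:
   - analyse week-52 SBP by ANCOVA with arm, baseline SBP and the other listed covariates; or
   - keep the baseline row, remove baseline BP from that model's covariates, constrain the arms to a common baseline mean and state the within-person covariance structure.

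Removing the covariate alone restores a valid SE but not the precision. Adding the intermediate visits is optional and not needed to correct the problem. The cost is a change of wording: the readings are already scheduled, and the sample size and power text can stay.

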#### Analysis of Cost-Effectiveness Data

Cost-effectiveness studies focused on mHealth interventions, specifically within the context of HTN, are lacking from the literature [40]. We will evaluate the cost-effectiveness of MI-BP using data from within the trial (aim 3); however, since HTN is a long-term chronic disease, the observed outcomes for the patients may not capture the entire benefit of the intervention. As such, we will also use a modeling approach to simulate patient lifetime outcomes, given their health status and trajectories at the end of the trial. We hypothesize that MI-BP will be cost-effective compared with usual care.

Costs will be prospectively collected from DMC, which serves most of the health needs of enrolled individuals. For the within-trial cost-effectiveness analysis, we will use ED, pharmacy, outpatient, estimated patient costs, and hospital cost data. Quarterly SF-12 assessments will be converted into utility measures using the methods of Brazier et al [41] and aggregated over the year to calculate quality adjusted life years (QALYs), a standard health-economic measure to compare across interventions. Total costs and total QALYs will be calculated for both arms. The MI-BP arm will be compared with usual care using an Incremental Cost-Effectiveness Ratio, a measure that compares health value for money. Bootstrapping will be used to assess uncertainty around the mean estimates, and it will be used to create cost-effectiveness acceptability curves [42].

For the long-term cost-effectiveness analysis, we will create a mathematical model of long-term quality of life and mortality because of HTN, which will be based upon other models in the literature, such as the approach used by Smith-Spangler et al [43], which modeled the relationship between SBP and long-term heart attack and stroke using a logistic risk function based on the Framingham data. Costs of disease states such as heart attacks and strokes will be taken from extant literature and databases such as the Medical Expenditure Panel Survey and Healthcare Cost and Utilization Project of the Agency for Healthcare Research and Quality. Health utilities will be taken both from the utilities collected and the medical literature (particularly for heart attacks and strokes). The models will begin with the health state of the participants at the end of the trial and will model health outcomes into the future. We will explore various assumptions about the durability of BP changes (eg, continuing improvement, stable BP, regression to prestudy BP levels). These cost-effectiveness analyses will follow standard guidelines for a *reference case* analysis, while the modeling approach and analysis will follow recent guidelines [44-46].

In addition to analyses for our stated aims, we also intend to conduct analyses to look at the patterns of MI-BP use that are associated with improved outcomes. For each of our self-monitoring behaviors (BP, physical activity, sodium intake, and medication adherence), we will calculate an overall utilization rate by dividing the number of logged data points by the total number of expected data points. Adherence to behavioral self-monitoring uptake for each activity will be compared within the MI-BP arm by means of count regression with the number of adherence instances (among the repeated observations) as outcome. Models will be controlled for variables similar to those in aim 1. To investigate whether better adherence to the self-monitoring uptake corresponds to an improvement in BP, we shall use a mixed-model analysis similar to that in aim 1 with BP measure as outcome and adherence as time-dependent binary covariates. Different self-monitoring behavioral components will simultaneously be used in the same model.

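### The within-trial cost-effectiveness procedure states no adjustment of the QALY difference for baseline SF-12 utility, although that utility is collected before randomisation and adjustment would gain precision at no cost

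*Protocol article*

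**What the plan says.** The section Analysis of Cost-Effectiveness Data describes the within-trial analysis in sequence. Quarterly SF-12 assessments become utilities, and these are aggregated over the year into QALYs. Then "Total costs and total QALYs will be calculated for both arms". Next, "The MI-BP arm will be compared with usual care using an Incremental Cost-Effectiveness Ratio". Finally, "Bootstrapping will be used to assess uncertainty around the mean estimates", and the bootstrap also supplies the acceptability curves. No covariate is named at any step.

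The data for an adjustment exist. Additional Health Measures lists "functional status using the 12-Item Short-Form Health Survey (SF-12) at baseline and weeks 13, 26, 39, and 52". Procedures places baseline data collection at week 0 and randomisation at week 2, so the baseline SF-12 precedes allocation.

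Elsewhere the article says when it adjusts. Under Analysis of Blood Pressure Control, the model for BP control includes "baseline levels of functional status, health literacy, HTN knowledge, self-efficacy, and baseline BP at randomization", and the SBP model takes over the same subject-level characteristics. The additional app-usage analyses are also to be controlled for covariates like those of aim 1. Aim 3 has no such sentence.

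**The concern.** A person's QALY total depends strongly on the utility at entry, both because baseline utility may be one term of the sum and because later utilities correlate with it. If the arms differ at baseline by chance, a raw difference in QALYs takes over part of that difference. Randomisation is stratified by sex only, so the design does nothing specific to balance baseline utility.

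The QALY difference is the denominator of the ratio, so noise there matters more than in an ordinary mean comparison: a small or uncertain denominator makes the ratio unstable and flattens the acceptability curve. As the article reads, baseline SF-12 is a covariate for blood pressure but is not stated as one for the outcome derived from SF-12 itself.

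**Working it through.** **The plan's own figures.** The article gives no utility SD, utility correlation, expected QALY gain or cost variance, so there is no economic figure to reproduce. The sample size used below does reproduce. For 30% against 47.5%, two-sided 5% and 90% power, the pooled two-proportion formula without continuity correction gives 161 per arm (power at 161 is 90.04%). The only correlation in the article, "along with an intra-subject correlation of 0.5", belongs to SBP.

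**Assumptions.** Equal correlation ρ between any two SF-12 utility assessments, taken from 0.3 to 0.7; constant variance s² over time; and one of two constructions of the QALY, since the article does not fix it.

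**Construction A: trapezoid over weeks 0, 13, 26, 39 and 52.** The weights are 1/8, 1/4, 1/4, 1/4, 1/8. Their sum of squares is 2(1/64) + 3(1/16) = 0.21875.

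- Var(Q)/s² = 0.21875 + 0.78125ρ
- Cov(Q, baseline)/s² = 0.125 + 0.875ρ. This is also the share of a baseline difference that passes into the raw QALY difference.
- Share of variance removed by adjustment: R² = (0.125 + 0.875ρ)² / (0.21875 + 0.78125ρ)
- Reduction in standard error: 1 − √(1 − R²)

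Example at ρ = 0.5: 0.5625² / 0.609375 = 0.519, and 1 − √0.481 = 0.307.

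**Construction B: the four follow-up assessments only, weight 1/4 each.** R² = ρ² / (0.25 + 0.75ρ). At ρ = 0.5: 0.25 / 0.625 = 0.40.

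| ρ (assumed) | A: share carried over | A: variance removed | A: SE reduction | B: variance removed | B: SE reduction |
|---|---|---|---|---|---|
| 0.3 | 0.39 | 33% | 18% | 19% | 10% |
| 0.4 | 0.48 | 42% | 24% | 29% | 16% |
| 0.5 | 0.56 | 52% | 31% | 40% | 23% |
| 0.6 | 0.65 | 61% | 38% | 51% | 30% |
| 0.7 | 0.74 | 71% | 46% | 63% | 39% |

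Half of the variance is removed only from ρ of about 0.48 under A and about 0.59 under B.

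**In terms of sample size.** To match an adjusted analysis with 161 per arm, a raw analysis under A needs 161/(1 − R²) per arm: 241 at ρ = 0.3, 335 at 0.5 and 556 at 0.7.

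**In QALY units.** The chance baseline difference has standard error SD × √(2/161). For assumed utility SDs of 0.08, 0.12 and 0.16 this is 0.0089, 0.0134 and 0.0178. At ρ = 0.5 under A, 0.5625 of it is carried over: 0.0050, 0.0075 and 0.0100 QALY (one standard error).

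**Other correlation structure.** If correlation decays exponentially with time and ρ is the baseline-to-week-52 value, R² at 0.3, 0.5 and 0.7 is 50%, 65% and 80% under A, and 35%, 53% and 72% under B. The gain is then larger.

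**The case against.** The strongest reply is that the article is condensed and never says that the comparison is unadjusted. Calculating QALY totals is compatible with using each person's total as the outcome of a regression. Covariates for aim 2 are not listed either, so the gap in aim 3 may be abbreviation. The article also states: "These cost-effectiveness analyses will follow standard guidelines for a" reference-case analysis, and the adjustment may sit in a fuller plan. This stands to the extent that a deliberate choice against adjustment cannot be read into the text. It does not remove the point: the section sets out a complete sequence from utilities to bootstrap, and anyone following it as written would compare raw means.

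Three stronger readings are tempting, and the documents do not support them.

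- A reader might infer that half or more of the precision is lost. That needs a utility correlation of about 0.5 to 0.6 or higher, depending on how the QALY is formed, and the article gives neither the correlation nor the construction. Precision must also be read as inverse variance: at ρ = 0.5 under the trapezoid the standard error falls by 31%.
- A reader might infer that the raw analysis is biased or invalid. Under randomisation it is unbiased, and the bootstrap already includes chance baseline imbalance in its spread.
- A reader might infer that imbalance would equal the treatment effect or reverse the sign of the ratio. The article states no expected QALY gain, utility SD or cost variance, so this cannot be shown.

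**Conclusion.** The point holds as a matter of efficiency. The stated procedure contains no adjustment for baseline SF-12 utility. Followed as written, it leaves chance baseline imbalance in the QALY difference and gives a wider interval than the same data allow. Adjustment would remove about 33% to 71% of the variance of the QALY difference (standard error 18% to 46% smaller) if QALYs are a trapezoid over five assessments, and about 19% to 63% if baseline is outside the sum. Both ranges rest on assumed equal correlations of 0.3 to 0.7. The gain is worth having across the whole range, but its size is not known from the article. The effect on the ratio and acceptability curve cannot be quantified without cost variances. The coprimary blood pressure analyses are not affected.

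**What to change.** State in the cost-effectiveness section, or in the analysis plan if it is not already there, that within each bootstrap resample:

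1. incremental QALYs are estimated by regressing individual QALYs on arm, baseline SF-12 utility and sex (the stratification factor);
2. incremental cost is estimated in the same resample, so that the correlation between cost and QALY is kept;
3. the ratio and the acceptability curve are built from these differences.

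State also how QALYs are formed from the five assessments, including whether baseline enters the sum. No new data, visits or participants are needed, because baseline SF-12 is already collected. The cost is a few lines of text and of code. If adjustment is already planned elsewhere, one sentence saying so settles the point.
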